### Secondary endpoints

Intracranial progression-free survival (IC-PFS), defined as intracranial PFS at initially treated and at new sites.OS, defined as the time from the date of randomization to death from any cause.Toxicity, assessed by the National Cancer Institute Common Terminology Criteria for Adverse Events (CTCAE) version 5.0.Non-worsening of Karnofsky performance status (KPS), defined as the time from randomization to decline of KPS from any cause.Non-worsening of mini mental status examination (MMSE), defined as the time from randomization to decline of MMSE from any cause.

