### Follow-up evaluation, assessment of efficacy, and data collection

Patients will be seen at 1 and 3 months after SRT and every 3 months thereafter. At each visit, physical examination, KPS, JCS, toxicities, and MRI of the brain are evaluated. MMSE is evaluated every 6 months after SRT. Since poorly timed MRI may be required depending on symptom, the time of MRI at plus or minus 1 month is allowed. The adverse events will be evaluated using CTCAE ver. 5.0. Table 1 shows the follow-up schedule. After progression at an intracranial site, additional treatment (e.g., WBRT) is at the discretion of the radiation oncologists. Anonymized data will be transmitted to the principal investigator from participating centres via the case reporting form. Anonymized data will be collected before SRT (baseline) and at 1 and 3 months after SRT and every 3 months thereafter according to Table 1. When any treatment-related death, any Grade 4 toxicity, and any death during the SRT periods or within 30 days of SRT is observed, the toxicity reporting form will be transmitted to the principal investigator from participating centres.

**Table 1 Tab1:** Pre- and post-treatment evaluation and assessment of efficacy

	Baseline	Treatment	Follow-up after				
Assessment^a^			1 M	3 M	6 M	Every 3 M thereafter	Every 6 M thereafter
Medical history	✓						
Physical examination	✓		✓	✓	✓	✓	
CT or PET-CT^b^	✓						
KPS	✓		✓	✓	✓	✓	
JCS	✓		✓	✓	✓	✓	
MMSE	✓				✓		✓
Brain MRI	✓		✓	✓	✓	✓	
Adverse events		✓	✓	✓	✓	✓	

Footnotes: *M* Months, *CT* Computed tomography, *PET-CT*
^18^F-fluorodeoxyglucose positron emission tomography-computed tomography, *KPS* Karnofsky performance status, *JCS* Japan Coma Scale, *MMSE* Mini mental status examination, *MRI* Magnetic resonance imaging

^a^Extra imaging outside of the study schedule is allowed per the discretion of the physician

^b^Either enhanced CT or PET-CT is required

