### Secondary endpoints

The IC-PFS rate will be calculated using the Kaplan-Meier method and differences will be compared using the stratified log-rank test. Only development of initially treated sites and new BM will be treated as event and death will not be considered to be competing event. When enrolled patient dies, the data at the last follow up will be used to calculate the IC-PFS rate. The OS rate will be calculated using the Kaplan-Meier method and differences will be compared using the stratified log-rank test. OS was defined as the time from the date of randomization to death from any cause.

The rates of grade 2 or higher toxicity will be compared between groups using the Fisher’s Exact Test. The non-worsening of KPS and MMSE scores at 6- and 12-months post-enrollment will be measured with differences between groups tested using the Fisher’s Exact Test. When enrolled patient dies, the data at the last follow up will be used. For KPS, a decrease in KPS of ≥10% will be considered a decline in KPS and sensitivity analysis will be performed. For MMSE, a decrease in MMSE score of ≥3 points will be considered a decline in cognitive function and sensitivity analysis will be performed.

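### Non-worsening of KPS and MMSE is defined as a time to decline but tested as a proportion at 6 and 12 months, so the planned test does not analyse the stated endpoint

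*Protocol article*

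**What the plan says.** All places are in the protocol article.

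- **Methods/design, Secondary endpoints.** Non-worsening of KPS is "defined as the time from randomization to decline of KPS from any cause"; non-worsening of MMSE is "defined as the time from randomization to decline of MMSE from any cause". Neither definition mentions death.
- **Statistical analysis, Secondary endpoints.** "The non-worsening of KPS and MMSE scores at 6- and 12-months post-enrollment will be measured with differences between groups tested using the" Fisher's exact test. Then: "When enrolled patient dies, the data at the last follow up will be used". The thresholds are "a decrease in KPS of ≥10% will be considered a decline in KPS" and "a decrease in MMSE score of ≥3 points will be considered a decline in cognitive function". A sensitivity analysis is announced for each scale but not described. The same section plans Kaplan-Meier estimates and a stratified log-rank test for IC-PFS and OS.
- **Follow-up evaluation, assessment of efficacy, and data collection.** "Patients will be seen at 1 and 3 months after SRT and every 3 months thereafter", with KPS taken at each visit, while "MMSE is evaluated every 6 months after SRT". Table 1 shows no MMSE between baseline and 6 months.
- **Sample size.** 1-year OS of 50%, 35 patients per arm, two-sided alpha 0.20. No decline rate, effect size, alpha or power is given for KPS or MMSE.

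**The concern.** One section defines a duration and the other tests a status at two dates. These are different endpoints, and the same patient can be an event under one and not under the other. An analyst following the article could report a time-to-decline result or any of four fixed-date p-values (two scales, two dates) and call each of them prespecified, in an open-label trial.

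The rule for deaths makes the difference larger. In a Kaplan-Meier analysis, using the last follow-up data of a patient who dies amounts to censoring. In a fixed-date proportion, the same rule carries the last score forward, so a patient who dies without a recorded decline is scored as a success. With half the patients expected to die within a year, that is not a rare case.

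**Working it through.** **1. The plan's own figure.** The only stated size is 70 patients, for IC-LC. With exponential hazards λ₁ = −ln 0.70 = 0.357 and λ₂ = −ln 0.90 = 0.105 per year, death as censoring at μ = −ln 0.50 = 0.693, uniform accrual over 4 years and 5 years in total:

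n per arm = [z₀.₉₀√(2φ(λ̄)) + z₀.₈₀√(φ(λ₁)+φ(λ₂))]² / (λ₁−λ₂)², where φ(λ) = λ²/P(event).

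This gives 34.8 per arm (69.7 in total) without loss and 35.1 per arm (70.3) with 5% loss over the trial. The stated 70 reproduces, with deaths censored. It carries no information on KPS or MMSE.

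**2. Definition and test side by side.**

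| Patient | Time to decline, as defined | Proportion at 6 and 12 months, as tested |
|---|---|---|
| First decline at month 15 | event | never counts |
| Dies at month 4; only a baseline MMSE | no event observed; no MMSE follow-up to contribute | not worsened at both dates |

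**3. How often the second case arises.** With 1-year OS of 50% and a constant hazard (assumed), 6-month mortality is 1 − 0.5^0.5 = 0.293. That is 0.293 × 35 ≈ 10 patients per arm.

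**4. Power.** Because the documents give no decline rates, 1-year non-worsening was assumed. Simulation settings: 35 per arm, 1,000 runs per scenario, exponential decline detected at the Table 1 visits, 1-year OS 50%, about 5% loss per year, staggered entry. An unstratified log-rank test on time to decline over all follow-up was compared with Fisher's test using the last value for deaths. Relative loss = 1 − Fisher power / log-rank power. Two-sided alpha 0.20:

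| Scale, assumed 1-year rates | Log-rank | Fisher 12 m | Fisher 6 m | Loss 12 m | Loss 6 m |
|---|---|---|---|---|---|
| KPS 50 / 70% | 64.8% | 44.2% | 34.2% | 32% | 47% |
| KPS 40 / 60% | 60.1% | 39.5% | 34.7% | 34% | 42% |
| KPS 50 / 80% | 87.1% | 70.4% | 55.7% | 19% | 36% |
| KPS 60 / 75% | 47.6% | 30.0% | 25.1% | 37% | 47% |
| MMSE 70 / 90% | 75.0% | 53.3% | 31.6% | 29% | 58% |
| MMSE 50 / 70% | 60.9% | 38.4% | 29.4% | 37% | 52% |
| MMSE 40 / 60% | 58.2% | 36.2% | 29.5% | 38% | 49% |
| MMSE 50 / 80% | 84.2% | 62.0% | 52.4% | 26% | 38% |
| MMSE 60 / 75% | 45.6% | 28.3% | 21.2% | 38% | 54% |

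KPS at 70 / 90% gave losses of 31% and 54%. The ranges are therefore 19–38% at 12 months and 36–58% at 6 months. If only survivors are analysed at 12 months, the loss is 26–45%. At alpha 0.05, with the last value for deaths, it is 40–58% and 59–86%.

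**5. Where the loss comes from.** For KPS 50 / 70%, a log-rank test cut off at 12 months has 56.2% power. Of the 64.8 − 44.2 = 20.6 points lost at 12 months, 64.8 − 56.2 = 8.6 are follow-up after 12 months. The other 56.2 − 44.2 = 12.0 come from replacing a time by a status, from the rule for deaths and from the conservatism of Fisher's test. Under no effect, Fisher's 12-month test rejected in 12.0% of runs and the log-rank test in 21.9%, at a nominal 20%, so the comparison slightly flatters the log-rank test.

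**The case against.** **Fixed-date proportions are legitimate for unpowered secondary endpoints.** This is true, and rewording the definitions as proportions at 6 and 12 months would also remove the contradiction. It would leave early deaths scored as MMSE successes and later declines unused, so it is the weaker repair.

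**A reader might infer that the test wastes about half the power.** The documents do not support a general figure. Modelling decline or death as one event, with hazard 1.05 per year and HR 0.6, does give 25% for Fisher's test at 12 months against 50% for the log-rank test at alpha 0.05. But 0.05 is not a level the protocol sets for these scales; at 0.20 the same model gives 50% against 74%, a loss of 1 − 50/74 = 32%. It also implies a total Arm 2 hazard of 0.6 × 1.05 = 0.63, below the death hazard of 0.693 that 50% 1-year OS implies. That requires a survival benefit, and the protocol assumes a single OS.

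**A reader might infer that death should be added to the event.** Neither definition includes it, and it can cost power. With equal survival, an Arm 1 decline hazard of 0.357 per year and alpha 0.20, the composite log-rank test has 24% power against 25% for 12-month Fisher at a decline HR of 0.6, and 36% against 57% at 0.295. The decline-only log-rank test has 42% and 81%.

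**A reader might infer that KPS visits before each date are discarded**, for example a drop at month 3 that recovers by month 6. The article does not say whether non-worsening at a date means status on that day or no decline up to it. On the second reading the earlier visits count, so the point does not rest on this.

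**The clock.** The dates run from enrollment and the visits from SRT, but SRT starts within 14 days of randomization and lasts 3 or 8 days. The shift is at most about 14 + 8 = 22 days. This is minor, though a strict 6-month cut-off would usually precede the first post-SRT MMSE.

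**Conclusion.** The contradiction stands on the text alone and needs no assumption: the definition is a duration, the test is on a status, and both are printed in the same article. It is not a detail that an analysis plan could fill in without overriding one of the two sections.

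Two consequences are firm in direction. Declines first seen after 12 months are never used. Patients who die before the 6-month MMSE are scored as not worsened; the figure of about 29% rests on the 50% 1-year OS and a constant hazard.

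Fisher's test had less power than the decline-only log-rank test in every scenario tried. The size of the loss (about one fifth to two fifths at 12 months, one third to three fifths at 6 months, at alpha 0.20) rests on assumed decline rates and an unstratified log-rank test, and should be quoted only as a range. The primary endpoint and the sample size are unaffected. The point should be corrected before the final analysis.

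**What to change.** In Statistical analysis, Secondary endpoints, replace the Fisher tests for KPS and MMSE with the following:

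- Analyse each scale as time from randomization to first decline (KPS by 10% or more; MMSE by 3 points or more), with Kaplan-Meier curves and the stratified log-rank test already planned for IC-PFS and OS.
- Censor patients who die without decline at their last assessment, in line with the rule for IC-LC and IC-PFS.
- Report time to decline or death as a sensitivity analysis only. It can serve as the one already announced for each scale.
- Keep the 6- and 12-month proportions as description, tied to the scheduled post-SRT visits.

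**Cost.** This is a wording change. The assessments are already scheduled, no interim analysis is planned and data collection runs to March 2027, so it can be made before the final analysis.

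**Downside.** Censoring at death assumes that death carries no information about decline, which is doubtful in this population; the decline-or-death analysis shows how far the result depends on it. Patients who die before the first post-SRT MMSE contribute no information on MMSE decline, and the report should give their number by arm.

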### Sample size

We use a randomized phase II screening design, with a two-sided α of 0.20 and a power of 80% as recommended for our current study [12]. In a phase II screening design, the α level is set higher than the level of a phase III design (i.e., 0.05). Even if the phase II trial is positive (i.e., *p* < 0.20), that is not considered conclusive without a subsequent phase III trial. The results of the previous study of irradiation at intervals demonstrated a 1-year IC-LC of 93% [13]. Assuming a 1-year IC-LC of 70% for Arm 1 (consecutive daily irradiation) and 90% for Arm 2 (irradiation at two- to three-day intervals) and a 1-year OS of 50% for target patients, with 80% power, alpha of 0.20, an 5% lost follow-up rate, accrual time of 4 years and a total trial time of 5 years, 70 patients will be required (35 in Arm 1 and 35 in Arm 2). The secretariat of the study will contact all co-investigators to facilitate enrollment regularly.

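### Scoring patients who die on their last KPS or MMSE value counts those without a recorded decline as non-worsened, which inflates both secondary endpoints and can favour the arm with more deaths

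*Protocol article*

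**What the plan says.** All places are in the protocol article.

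- **Analysis** (Statistical analysis, Secondary endpoints): "The non-worsening of KPS and MMSE scores at 6- and 12-months post-enrollment will be measured with differences between groups tested" by Fisher's exact test.
- **Deaths** (same paragraph): "When enrolled patient dies, the data at the last follow up will be used. For KPS", where the last two words open the sentence on the KPS threshold.
- **Decline** (same paragraph): the KPS threshold reads "a decrease in KPS of ≥10% will be considered a decline in KPS and sensitivity analysis will be performed". The MMSE threshold is a fall of at least 3 points, again with a sensitivity analysis promised. Neither threshold includes death, and the content of the sensitivity analyses is not given.
- **Endpoint definitions** (Methods/design, Secondary endpoints): KPS is "defined as the time from randomization to decline of KPS from any cause" and MMSE is "defined as the time from randomization to decline of MMSE from any cause". These are times to an event, whereas the analysis is of proportions at fixed times.
- **Schedule** (Follow-up evaluation and Table 1): KPS is recorded at baseline, 1 and 3 months, then every 3 months. For MMSE, "MMSE is evaluated every 6 months after SRT", in addition to baseline.
- **Mortality** (Sample size): the design assumes "a 1-year OS of 50% for target patients", with 35 patients per arm.

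**The concern.** For local control and intracranial progression the article has a similar sentence on deaths. There it can be read as censoring at the last assessment, because those endpoints use Kaplan-Meier estimates and a log-rank test. Fisher's exact test has no censoring: each patient in the table is either worsened or non-worsened. Under the stated rule a patient who has died is classified by the last score, and one who died with no decline on record enters as a success.

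The design itself expects half the patients to have died by 12 months, so this concerns a large share of each arm. Two things are at stake. The reported proportions overstate how many patients are alive with preserved function. And if survival differs between the arms, the functional comparison can point towards the arm in which more patients died. These are the trial's only planned comparisons of performance status and cognition.

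**Working it through.** The article gives no expected figure for KPS or MMSE non-worsening, so there is none to reproduce. The check applies the stated rule to the protocol's survival assumption and visit schedule.

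**Inputs from the article:** 1-year survival 50%; 35 per arm; MMSE at 0, 6 and 12 months; KPS at 0, 1, 3, 6, 9 and 12 months.

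**Assumed inputs:** exponential survival and decline; decline persists once it occurs; 70% decline-free at 12 months, so 0.7^0.5 = 0.837 at 6 months; decline independent of death unless stated; baseline used when no later MMSE exists; for the between-arm example, 1-year survival of 40% and 60%.

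**Step 1. Deaths before the first post-baseline MMSE.** 1 − 0.5^0.5 = 0.293, and 0.293 × 35 = 10.3 patients per arm. Their last value is baseline, the change is zero, and they are non-worsened. Deaths between 6 and 12 months: 0.707 − 0.5 = 0.207.

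**Step 2. MMSE at 12 months, survival 50%.**
- Rule: 0.293 + 0.207 × 0.837 + 0.5 × 0.70 = 0.816, or 82%.
- Alive and non-worsened: 0.5 × 0.70 = 35%.

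**Step 3. Unequal survival, same decline rate in both arms.**

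| 1-year survival | Died before month 6 | Died in months 6–12 | Rule reports | Alive and non-worsened |
|---|---|---|---|---|
| 40% | 0.368 | 0.232 | 0.368 + 0.232 × 0.837 + 0.28 = 84% | 0.4 × 0.7 = 28% |
| 60% | 0.225 | 0.175 | 0.225 + 0.175 × 0.837 + 0.42 = 79% | 0.6 × 0.7 = 42% |

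The rule puts the arm with more deaths 5 points ahead.

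**Step 4. When the direction reverses.** Let S be survival, d the decline rate among survivors, and q the share of the dead whose last recorded value was already a decline. The rule reports

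S(1 − d) + (1 − S)(1 − q) = (1 − q) − S(d − q).

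With d and q equal in both arms, the advantage of the higher-mortality arm is (difference in S) × (d − q). For S = 60% versus 40% and d = 30%, this is 0.2 × (0.30 − q):

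| q | Advantage of the arm with more deaths |
|---|---|
| 0 | +6 points |
| 0.25 | +1 point |
| 0.50 | −4 points |
| 0.75 | −9 points |

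The rule favours the arm with more deaths when q < d and disfavours it when q > d.

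**Step 5. KPS against MMSE, and death linked to decline.** This is a simulation on the visit schedule, with a different assumed decline rate (60% decline-free at 1 year, the same decline hazard in both arms). Figures are 12-month non-worsening under the rule, for survival of 60% versus 40%.

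| Scenario | KPS | MMSE | Alive and non-worsened |
|---|---|---|---|
| Death independent of decline | 70% vs 75% | 72% vs 79% | 36% vs 24% |
| Death hazard triples after decline | 70% vs 76% | 75% vs 83% | 41% vs 30% |

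Across these runs and a run at 50% survival, 72–86% of the dead are counted as non-worsened for KPS and 84–91% for MMSE. The effect is smaller for KPS, because more frequent visits catch more declines before death, but it does not disappear.

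**The case against.** **The baseline reading is an inference.** The rule refers to data at the last follow-up, and Table 1 separates baseline from follow-up. A patient who dies before month 6 has no follow-up MMSE and could be treated as unevaluable. Removing those patients from Step 3 gives (0.232 × 0.837 + 0.28) / 0.632 = 75% against (0.175 × 0.837 + 0.42) / 0.775 = 73%, a gap of 2 points instead of 5. This stands: using baseline is the natural reading, not the only one. Deaths after month 6 are still scored on an earlier value under either reading.

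**Not every death counts as a success.** A reader might infer that all patients who die are scored non-worsened. The text does not support that: a patient whose last value already met the threshold counts as worsened, and KPS visits are frequent enough to record many such declines.

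**The direction is not fixed.** A reader might also infer that the rule will always favour the arm with more deaths. Step 4 shows that it need not. The article gives a single survival figure for both arms; with equal survival and equal decline behaviour there is no between-arm bias. Even at 40% versus 60%, the gap is about 2 patients (30/35 versus 28/35, Fisher p = 0.75).

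**The composite answers another question.** In Step 3 the arms do not differ in decline, yet alive-and-not-worsened differs by 14 points, entirely through mortality, which overall survival already reports. This stands, and it is why decline among survivors must be shown beside it.

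**Mitigation in the text.** The promised sensitivity analyses follow the decline thresholds and do not mention death. The phrase on any cause in the endpoint definitions might be read to include death, but the explicit rule scores deaths on the last value. Neither removes the problem.

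**Conclusion.** The concern holds in a limited form. As written, the rule counts as non-worsened every patient who dies without a recorded decline, and so overstates the share alive without decline in both arms: for MMSE at 12 months, 82% against 35% under the stated assumptions. The between-arm effect is conditional. It needs a survival difference, and it favours the higher-mortality arm only while recorded decline is rarer among the dead than among survivors; the example is 84% versus 79%. MMSE is affected most, KPS less.

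Only the 50% survival figure, the sample size and the visit schedule come from the article. The exponential form, the decline rates, the survival split and the use of baseline as the last MMSE are assumptions. The primary endpoint and its conclusion are untouched, and overall survival is reported separately. Severity is moderate.

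**What to change.** In Statistical analysis, Secondary endpoints:

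1. Delete the sentence on patients who die as it applies to KPS and MMSE.
2. Analyse the proportion alive and not worsened at 6 and 12 months, with death before the time point counted as not meeting the endpoint. Alternatively, analyse time to decline or death, which also brings the analysis closer to the time-to-event definitions in Methods/design.
3. Report decline among survivors at each time point alongside, with the numbers dead and not assessed per arm, so that a mortality difference is not read as a functional one.

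The cost is a change to one sentence and an added table, with no new data, visits or patients. The reported proportions will be lower, and the composite partly reflects overall survival. Follow-up and data collection are planned to run to March 2027, so the change should be fixed before the data are analysed.

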### Pre-treatment evaluation

Re-staging is performed within 8 weeks prior to randomization. ^18^F-fluorodeoxyglucose (18-FDG) positron emission tomography (PET) -computed tomography (CT) or a contrast-enhanced CT of the neck to the pelvis is recommended for the evaluation of extracranial metastases. In cases where a contrast agent is unavailable due to impaired renal function or allergic intolerance, a plain CT is allowed. Before random assignment within 2 weeks, all patients are necessary to be evaluated by an MRI of the brain. MRI is performed with a gadolinium-enhanced T1 3D Fast Field Echo and 3D reconstruction of the axial, sagittal, and coronal planes with 1 mm slice thickness (thin-slice MRI). In addition, each patient undergoes a baseline evaluation consisted of medical history including prior treatments of cancer and concomitant anticancer medications, symptom burden, KPS, Japan Coma Scale (JCS), and MMSE.

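### MMSE is compared between arms only as a fall of at least 3 points (yes/no) by Fisher's exact test; a pre-specified analysis of the score should stand beside it

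*Protocol article*

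**What the plan says.** - **Definition of decline** (Statistical analysis, Secondary endpoints): "For MMSE, a decrease in MMSE score of ≥3 points will be considered a decline in cognitive function and sensitivity analysis will be performed". The content of that sensitivity analysis is not given.
- **Test** (same section): "The non-worsening of KPS and MMSE scores at 6- and 12-months post-enrollment will be measured with differences between groups tested using the Fisher’s Exact Test". For patients who die, the data from the last follow-up are used.
- **Data available**: baseline evaluation includes MMSE (Pre-treatment evaluation: "symptom burden, KPS, Japan Coma Scale (JCS), and MMSE"), and afterwards "MMSE is evaluated every 6 months after SRT" (Follow-up evaluation; Table 1 agrees).
- **Endpoint list** (Methods/design, Secondary endpoints): non-worsening of MMSE is there "defined as the time from randomization to decline of MMSE from any cause". That a time there becomes a proportion in the analysis section is a separate matter and is not pursued here.

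The article gives no SD, expected decline rate, target difference, alpha or power for MMSE.

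**The concern.** Once the score is cut at 3 points, a 2-point fall counts the same as an improvement, and a 3-point fall the same as a 12-point fall. Baseline enters only through the subtraction that forms the fall. The stratification factors, used in the log-rank tests, are not used here. Fisher's test is also conservative in small samples.

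The samples are small: 35 per arm with an assumed one-year survival of 50%. Cognition is a named secondary endpoint of a trial that sets out to describe the effect of the irradiation interval, toxicity included. If the only comparison has little chance of showing a moderate difference that the collected scores might show, a null result is hard to interpret.

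**Working it through.** **The plan's own figure.** There is none for MMSE. The 70 patients are sized on local control: with 14 events, an event probability of 0.213 and 5% loss, 14 / 0.213 / 0.95 = 69.2, hence 70. The figure depends on taking 14 events and has no bearing on MMSE.

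**Patients with an observed score.** Inputs from Sample size: 35 per arm, 5% loss, one-year survival 50%. Assuming exponential survival, S(6 months) = 0.5^0.5 = 0.71.
- 6 months: 35 × 0.95 × 0.71 = 23.6, about 24 per arm.
- 12 months: 35 × 0.95 × 0.50 = 16.6, about 17 per arm.

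**One case in full (all MMSE inputs assumed).** Change is normal and rounded to whole points, with mean −1 in one arm and −3 in the other and SD 3; 24 per arm, two-sided 0.05. After rounding, a fall of at least 3 means a change below −2.5.
- Decline rates: Φ((−2.5 + 1)/3) = Φ(−0.50) = 0.31, and Φ((−2.5 + 3)/3) = Φ(0.17) = 0.57.
- Fisher's exact test on 0.31 vs 0.57, summed over all outcomes: power 0.35.
- Uncorrected chi-square on the same cut: 0.47.
- t-test on change, effect 2/3 SD, noncentrality 0.667 × √12 = 2.31: 0.62.
- Simulated scores with baseline N(27, 2.5) capped at 30: ANCOVA 0.57 to 0.60 over repeat runs, rank test on change 0.55 to 0.58.

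Of the 22 to 25 points between Fisher and ANCOVA, about 12 (0.47 − 0.35) come from Fisher's conservatism. The other 10 to 13 come from the cut and the lack of adjustment.

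**Other mean-shift cases** (same baseline, two-sided 0.05):

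| n per arm | Extra loss | SD of change | Fisher on cut | ANCOVA |
|---|---|---|---|---|
| 24 | 2 | 2.5 | 0.48 | 0.74 |
| 24 | 1.5 | 4 | 0.11 | 0.22 |
| 17 | 2 | 3 | 0.23 | 0.46 |

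Over the grid (extra loss 1.5, 2, 2.5; SD 2.5, 3, 4; n = 17 and 24) the difference is roughly 10 to 28 points at 0.05 and 11 to 26 at 0.20, the trial's design alpha. Against an uncorrected chi-square on the same cut it is 2 to 14 points. With no true difference and nominal 0.05, Fisher rejects in 2 to 3% of trials and ANCOVA in about 5%.

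**Effect confined to a subset with falls.** The result now depends on the shape assumed.
- 40% vs 15% of patients falling by 5 or 8 points: the score analyses gain about 7 to 17 points over Fisher.
- 20% vs 45–50% falling by 3 points plus a skewed excess: ANCOVA is 1 to 7 points above Fisher and about 6 to 11 below an uncorrected chi-square on the cut.
- 20% vs 50% declining, mostly by 3 to 5 points but a quarter of decliners by 10 to 20; 24 per arm, 0.05: Fisher 0.49, ANCOVA 0.38 to 0.39, rank test 0.44. With 20% vs 45%: Fisher 0.36, ANCOVA 0.29.

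**Deaths kept in, as the plan says.** With 33 per arm, the 29% assumed dead by 6 months carrying baseline forward, extra loss 2 and SD 3: Fisher 0.26 vs ANCOVA 0.50 at 0.05, and 0.55 vs 0.78 at 0.20. The mean-shift result therefore does not rest on analysing survivors only.

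**The case against.** The strongest reply is that the cut defines the endpoint. The endpoint is non-worsening, which needs a threshold, and a proportion declining is easy to read. Replacing it by a mean difference would change the question and leave the named endpoint untested. This stands, and it is why the 3-point comparison should be kept.

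Second, the direction of the power difference depends on assumption. A few large falls among mostly stable patients is conceivable in brain metastases, and there ANCOVA can lose to the planned test. This also stands. It argues for a rank test beside the mean difference and against ANCOVA alone.

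Third, the promised sensitivity analysis may use the score, and its details may be in the full protocol. That is possible. As written, however, the sentence ties it to the definition of decline and does not say that the score will be analysed.

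Fourth, the endpoint is unpowered, and ANCOVA power in the 0.05 cases shown above is still only 0.22 to 0.74. This is true and limits the weight of the point.

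A reader might infer that the baseline value is discarded. It is not: a decrease needs a starting value and baseline MMSE is collected. What is missing is its use as a covariate.

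**Conclusion.** The point holds as a modest improvement. The stated between-arm comparison of MMSE uses only whether the score fell by 3 points. Under the assumed mean shifts this costs roughly 10 to 28 points of power at two-sided 0.05, and at SD 3 with an extra loss of 2 about half of that comes from Fisher's test itself.

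That range is not a property of the trial. A wider set of assumptions (SD 2.5 to 5, effects of 0.3 to 0.8 SD, 17 to 35 per arm) gives about 7 to 70 points against a t-test on change, and the subset scenarios give little loss or a reversal against ANCOVA.

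A reader might go further and conclude that the cut is an error or that ANCOVA should replace it. The article does not support either: nothing in it contradicts the cut, and no MMSE distribution is given from which one method could be shown to be better throughout. The defensible conclusion is that a pre-specified analysis of the score is worth adding.

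**What to change.** In Statistical analysis, Secondary endpoints:

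1. Keep the proportion with a fall of at least 3 points as the non-worsening comparison.
2. Add a pre-specified between-arm analysis of the MMSE score at 6 and 12 months: a stratified rank test on change from baseline, together with a mean difference adjusted for baseline MMSE and the two stratification factors, with its confidence interval.
3. State whether patients who died enter this analysis under the same last-data rule or are excluded, and show deaths by arm beside both results.

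This takes a sentence or two and needs no new visits, data or patients. The cost is one more unpowered secondary result, less direct to read than a proportion. If limited to survivors, it is not a comparison of all randomised patients; if the last-data rule is used, many 12-month values will predate death. Neither the rank test nor the adjusted difference resolves that, so the choice must be stated.
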